## Abstract

**Background:**

For complete revascularization, patients with diffuse coronary artery disease should have a coronary endarterectomy and a coronary artery bypass graft (CE-CABG). Sadly, CE can lead to a lack of endothelium, which raises the risk of thrombotic events. Even though daily dual antiplatelet therapies (DAPT) have been shown to reduce thrombotic events, the risk of perioperative thrombotic events is high during the high-risk period after CE-CABG, and there is no consistent protocol to bridge DAPT. This trial aims to compare safety and efficacy between tirofiban and heparin as DAPT bridging strategies after CE-CABG.

**Methods:**

In phase I, 266 patients undergoing CE-CABG will be randomly assigned to tirofiban and heparin treatment groups to compare the two treatments in terms of the primary safety endpoint, chest tube drainage in the first 24 h. If the phase I trial shows tirofiban non-inferiority, phase II will commence, in which an additional 464 patients will be randomly assigned. All 730 patients will be studied to compare major cardiovascular and cerebrovascular events (MACCEs) between the groups in the first 30 days after surgery.

**Discussion:**

Given the possible benefits of tirofiban administration after CE-CABG, this trial has the potential to advance the field of adult coronary heart surgery.

**Trial registration:**

chictr.org.cn, ChiCTR2200055697. Registered 6 January 2022. https://www.chictr.org.cn/com/25/showproj.aspx?proj=149451. Current version: 20,220,620.

## Administrative information

Note: the numbers in curly brackets in this protocol refer to SPIRIT checklist item numbers. The order of the items has been modified to group similar items (see http://www.equator-network.org/reporting-guidelines/spirit-2013-statement-defining-standard-protocol-items-for-clinical-trials/).

## Introduction

### Background and rationale {6a}

Creation of distal surgical anastomoses can be difficult in patients with severe complex or diffuse coronary artery disease (CAD) undergoing coronary artery bypass grafting (CABG). Incomplete revascularization can affect patient survival and quality of life [1]. Coronary endarterectomy (CE) was first introduced in 1957 by Bailey et al. and is now being performed as an adjunct with CABG (CE-CABG) in patients with diffuse CAD to achieve complete revascularization [2]. Although long-term survival is comparable between CE-CABG and CABG alone, early surgical outcomes related to postoperative myocardial infarction (POMI) and mortality are worse in those undergoing CE-CABG [3–5]. These patients mainly experience graft occlusion owing to thrombosis in endarterectomized regions. During endarterectomy, the vascular intima is carefully dissected and removed, which exposes the subendothelial tissue to blood flow, causing fibrin platelet mural thrombus and activation of the coagulation cascade [6–8]. Dual antiplatelet therapy (DAPT) and postoperative anticoagulation may play a role in avoiding POMI after CE-CABG.

Current clinical guidelines recommend DAPT as soon as feasible after CABG and continuation for at least 12 months [9]. However, the use of antithrombotic medication within 24 h of CE-CABG is controversial. Reported rates of hemorrhage, POMI, and short-term mortality after CE-CABG vary substantially between studies [10–12]. Some centers have begun to use a heparin infusion 4 h after surgery in patients undergoing CE if the chest tube output is less than 50 to 100 mL/h. However, the incidence of POMI appears to be relatively high even with early heparin infusion [10, 11].

Tirofiban is a small-molecule peptide that selectively inhibits fibrinogen–platelet GP IIb/IIIa binding and reduces ischemic events in patients with acute coronary syndrome (ACS) undergoing percutaneous coronary intervention [13, 14]. Since perioperative use of GP IIb/IIIa inhibitors does not increase surgical bleeding after CABG [15–17], we hypothesized that early tirofiban administration before initiation of DAPT reduces the incidence of thrombosis and POMI after CE-CABG but does not increase bleeding incidence or severity.

### Objectives {7}

The primary goal of the THACE-CABG trial is to demonstrate the safety of early tirofiban administration after CE-CABG (phase I). If safety is demonstrated, its efficacy in reducing the incidence of major cardiovascular and cerebrovascular events (MACCEs) will be evaluated in comparison to early heparin administration (phase II).

### Trial design {8}

The THACE-CABG trial is a multicenter prospective randomized controlled trial. Patients will be randomized into one of two parallel groups at a 1:1 allocation ratio: an experimental group (tirofiban) and a control group (heparin). The safety portion of the study is a noninferiority trial with a primary endpoint of cumulative chest tube drainage in the first 24 h after surgery. The efficacy portion of the study is a superiority trial that will evaluate MACCEs in the 30 days after surgery as the primary endpoint. MACCEs include all-cause death, nonfatal MI, nonfatal acute ischemic stroke, and early revascularization.

### Eligibility criteria {10}

Inclusion criteriaAge 18–80 years.Primary diagnosis of non-ST elevation ACS or stable ischemic heart disease and appropriate candidate for isolated CABG.Ability to understand the nature of the study and the study-related procedures and comply with them.Undergoing CE-CABG.Agreeable to provide written informed consent for surgery and study participation.

Exclusion criteriaSevere congestive heart failure (New York Heart Association class IV) or left ventricular ejection fraction ≤ 35%.Tumor or suspected tumor.Severe renal insufficiency (creatinine clearance < 30 mL/min) and/or chronic hemodialysis.Cirrhosis or positive serum HBsAg/HBeAg, HCV-RNA, or anti HCV antibodies.History of heparin/tirofiban allergy or thrombocytopenia after heparin/tirofiban.Coagulation dysfunction, history of platelet abnormality or thrombocytopenia (preoperative platelet count < 150,000/mm^3^).History of active internal hemorrhage, intracranial hemorrhage, or intracranial tumor, arteriovenous malformation, or aneurysm.History of gastrointestinal or urogenital bleeding in the 6 months prior to randomization.Stroke (any cause) or transient cerebral ischemia in the 6 months prior to randomization. Pregnancy or breastfeeding.Use of extra anticoagulation therapy, intra-aortic balloon pump, extracorporeal membrane oxygenation, or other circulatory support before, during, or in the first 2 h after surgery (individuals who experience excessive bleeding or require mechanical circulatory support and excessive anticoagulant medication within 2 h have intrinsic bleeding risks and are not candidates for further antithrombotic therapy).CE-CABG surgery failed. CE-CABG failure. Graft flow and pulsatility index (PI) are measured at the end of the operation before protamine administration. If PI ≥ 5, the graft requires re-anastomosis; if still ≥ 5 after excluding the influence of operative technique, the operation is considered to have failed.Chest tube bleeding > 150 mL in the first 2 h after surgery.New-onset abnormal Q wave in the ECG within 2 h after surgery (indicates POMI; tirofiban or heparin are started 2 h after surgery for reducing POMI, thus individuals already having POMI within 2 h will be eliminated).

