## Intervention description {11a}

### Standard procedure before randomization

Before surgery, patients hospitalized for isolated CABG will receive the following standard antithrombotic regimen: aspirin will be administered up to the day of the procedure; clopidogrel, ticagrelor, and prasugrel will be stopped at least 5, 5, and 7 days before, respectively.

CE-CABG will be performed by experienced surgeons via a median sternotomy utilizing either an on- or off-pump grafting technique. CE will be indicated for patients with: (1) a long, diffusely diseased coronary artery segment or severely calcified coronary artery, or (2) severe long-segment in-stent restenosis with or without major side branch occlusion [23]. CE is occasionally unanticipated prior to CABG surgery. CE-CABG is typically the last option for obtaining full revascularization. Patients who do not undergo CE have a better prognosis than those that do when antithrombotic medication is used according to current recommendations; therefore, they are not required to receive tirofiban therapy and will not be included.

Graft flow and PI will be assessed at the end of the operation before protamine administration using the VeriQ Flowmeter System (MediStim ASA, Horten, Norway), which is based on an ultrasonic transit time flow meter. If the PI is more than 5, the graft must be anastomosed again. If it remains above 5, the surgery is deemed a failure and the patient will be removed from the study.

After the procedure, protamine will be administered to reverse the heparin (100 IU heparin: 1 mg protamine) and the active coagulation time will be corrected to the pre-heparinization value of 5%. Chest tube blood loss will be evaluated 2 h after surgery; if < 150 mL, the patient will be randomized.

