### Randomization and intervention

Eligible patients will be randomized to either the heparin or tirofiban group in a 1:1 ratio utilizing an interactive online response system. Using the biased-coin minimization approach, a static randomization list will be created and applied taking three strata into consideration: research site, patient age group (< 70 and ≥ 70 years), and gender. Figure 1 depicts the enrollment and randomization procedures.

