**Fig. 1 Fig1:**
[figure not shown]
Study design. TIA, transient cerebral ischemia; IABP, intra-aortic balloon pump; ECMO, extracorporeal membrane oxygenation

Two hours after randomization, heparin (100 IU/kg) will be administered intravenously in 5 mL of 0.9% sodium chloride every 4 h in the heparin group. In the tirofiban group, tirofiban (0.05 g/kg/min) will be infused over 22 h using a micropump starting within 30 min of randomization. To maintain treatment blinding, a 5-mL volume of 0.9% sodium chloride will be administered to patients in the tirofiban group, and patients in the heparin group will receive an infusion of 0.9% sodium chloride via micropump. Only the nurses who prepared the fluids will know which are genuine medications. Once heparin or tirofiban stop at 24 h, DAPT will be initiated the next day of surgery and continued daily (ticagrelor 90 mg twice daily plus aspirin 100 mg daily in patients with platelet count ≥ 9 × 10^9^ cells/L; aspirin alone daily in patients with platelet count < 9 × 10^9^ cells/L). For patients who are unable to be extubated within 24 h, heparin or tirofiban will be continued until the patient is extubated, at which point DAPT will start. The timeline of antithrombotic drugs is showed in Fig. 2.

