**Fig. 2 Fig2:**
[figure not shown]
Timeline of antithrombotic drugs. DAPT, dual antiplatelet therapies

To ensure patient safety, heparin and tirofiban doses will be adjusted according to routine blood and coagulation parameters obtained 4 and 10 h after treatment initiation. If the platelet count is < 90,000/mm^3^ after a repeat test, tirofiban infusion will be discontinued. If the activated partial thromboplastin time increases to 2.5 to 3 times the normal upper limit value, the heparin or tirofiban dose will be halved; if more than 3 times, they will be discontinued. If the fibrinogen level decreases to < 1.0 g/L, heparin and tirofiban infusions will be discontinued and fresh frozen plasma will be administered.

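### As described in the text, the 2 h entry check has no post-operative platelet count, so a patient already below the protocol's own tirofiban stopping level can be randomised and started on the drug

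*Protocol article*

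**What the plan says.** Eligibility criteria {10} sets the platelet limit for entry before the operation: "Coagulation dysfunction, history of platelet abnormality or thrombocytopenia (preoperative platelet count < 150,000/mm^3". The same list contains criteria that can only be judged after surgery: failed graft flow, circulatory support or extra anticoagulation up to 2 h, chest tube loss over 2 h, and a new Q wave within 2 h. None of them is a platelet count.

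Standard procedure before randomization has the coagulation time corrected after protamine and then gives the trigger for entry: "Chest tube blood loss will be evaluated 2 h after surgery; if < 150 mL, the patient will be randomized". Randomization and intervention refers the reader to a flow chart ("Figure 1 depicts the enrollment and randomization procedures"), which is not shown in the text at hand. Table 2, the schedule of assessments, is not shown either.

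The text after Fig. 1 says that tirofiban "will be infused over 22 h using a micropump starting within 30 min of randomization". The text after Fig. 2 says that "heparin and tirofiban doses will be adjusted according to routine blood and coagulation parameters obtained 4 and 10 h after treatment initiation". It then gives the stopping rule: "If the platelet count is < 90,000/mm^3^ after a repeat test, tirofiban infusion will be discontinued".

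**The concern.** The entry rule and the stopping rule do not fit together. The protocol regards a count below 90,000/mm3 as a reason to stop tirofiban, yet no entry criterion in the text uses that level at the moment when the drug is about to start. The pre-operative limit cannot do this job, because cardiac surgery lies between that count and the first dose.

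The protocol already accepts the principle behind a second look. It re-screens at 2 h because patients who bleed heavily or need support by then are judged unsuitable for more antithrombotic treatment. A low post-operative platelet count is a reason of the same kind, and it is left out.

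What is at stake is patient safety. Someone a few hours out of cardiac surgery could be given a platelet inhibitor at a count at which the protocol itself would withdraw it.

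**Working it through.** The plan states no figure for this point, so there is nothing to reproduce. The check sets the steps between surgery and the first count in order and then does simple arithmetic.

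**Inputs**
- Pre-operative entry limit: 150,000/mm3 (Eligibility criteria {10}).
- Tirofiban stopping level: below 90,000/mm3, confirmed on repeat (text after Fig. 2).
- Entry decision: 2 h after surgery (Standard procedure before randomization).
- Tirofiban start: 0 to 30 min after randomisation; planned infusion 22 h (text after Fig. 1).
- First blood count described: 4 h after treatment starts, the next at 10 h (text after Fig. 2).

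**Sequence of checks**

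| Time | Check described | Platelet count? |
|---|---|---|
| Before surgery | Platelets at least 150,000/mm3 | Yes |
| End of surgery | Graft flow; coagulation time after protamine | No |
| Up to 2 h after surgery | Drainage, support or extra anticoagulation, Q wave | No |
| 2 to 2.5 h after surgery | Tirofiban starts | No |
| 6 to 6.5 h after surgery | Routine blood and coagulation tests | Yes |

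**Timing.** Start of tirofiban: 2 h + (0 to 0.5 h) = 2 to 2.5 h after surgery. First described count: a further 4 h, so 6 to 6.5 h after surgery.

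**Exposure before the rule acts.** If no earlier count is acted on: 4/22 = 240/1,320 min = 18% of the planned infusion, plus the time for the repeat test. If an earlier count is known and acted on, exposure is close to 0 h. The range is therefore 0 to about 4 h plus the repeat.

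**Fall needed to be below the stopping level.** Fall = 1 − 90/baseline, with the baseline in thousands per mm3:
- 150: 1 − 90/150 = 40%
- 175: 1 − 90/175 = 48.6%
- 200: 1 − 90/200 = 55%
- 250: 1 − 90/250 = 64%
- 300: 1 − 90/300 = 70%

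The actual fall must exceed these values. The documents give no distribution of baseline or post-operative counts, so the share of patients affected cannot be calculated.

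**The case against.** The strongest reply is that this is an argument from silence. Fig. 1 and Table 2 are where a blood count before randomisation would be expected to appear, and neither is shown. The article also plainly does not list every count. The choice between dual therapy and aspirin alone at about 24 h depends on a platelet count, yet the only sampling times given are 4 h and 10 h. The 4 h sample is described as a point for dose adjustment, not as the first count taken. A routine count may well be available earlier. This stands, and it is why the point is limited to the text and to the case in which no earlier count is acted on. It does not remove the point: the eligibility list and the 2 h check are written out in detail, and they say that the patient is randomised once the drainage condition is met.

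A second reply is that 150,000/mm3 at entry and 90,000/mm3 on treatment are compatible thresholds that leave room for a 40% fall. They are compatible as numbers. However, one is applied before the operation and the other, on the schedule described, only hours into the infusion.

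Third, there are partial safeguards: low drainage at 2 h, the undefined exclusion for coagulation dysfunction, and the researchers' freedom to withdraw patients (Criteria for discontinuing or modifying allocated interventions {11b}). They lower the risk, but none ties the 90,000/mm3 level to entry.

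A reader might also infer a stronger fault: that when a low count is already known, treatment would be stopped at once in one arm only. The platelet rule names tirofiban alone, whereas the neighbouring rules cover both drugs ("the heparin or tirofiban dose will be halved"; "If the fibrinogen level decreases to < 1.0 g/L, heparin and tirofiban infusions will be discontinued"). The documents do not support that reading. Under Concealment mechanism {16b} and Implementation {16c}, heparin patients receive saline labelled as tirofiban, and blinded staff give fluids by label. They would therefore stop the tirofiban-labelled infusion in either arm. Stopping on a known low count is also the safety rule working as intended.

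**Conclusion.** The point holds in a limited form. Followed as written, the 2 h check lets in a patient whose platelets have already fallen below 90,000/mm3. If no earlier count is acted on, a patient allocated to tirofiban can receive up to about 4 h of it, plus the repeat-test time, before the stopping rule acts.

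This rests on two assumptions: that the unseen Fig. 1, Table 2 or full protocol contain no platelet check before allocation, and that local routine practice does not supply one that is acted on. Neither can be tested from the documents. It should not be inferred that no post-operative count is ever taken before randomisation. Nor should it be inferred that the drainage or MACCE comparison is biased, since nothing in the text shows such an effect. With the frequency unknown and partial safeguards in place, the priority is low to moderate. The change is still worth making, because the trial's first aim is to show safety.

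**What to change.** Add one exclusion to Eligibility criteria {10} and to the 2 h check in Standard procedure before randomization: post-operative platelet count below 90,000/mm3, confirmed on repeat, applied to all patients before allocation. Use the routine post-operative sample where there is one; otherwise take one earlier sample, in time for the result to be ready at 2 h. Keep the 4 h and 10 h checks for falls on treatment. If Fig. 1 or the full protocol already contains such a check, stating it in these two sections is enough.

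The costs are small:
- A few more exclusions, including patients for whom the protocol states no platelet bar to heparin.
- Possibly one earlier blood sample.
- A short delay to randomisation and first dose when a repeat test is needed.
- A protocol amendment. Recruitment began on 1 September 2022 (Trial status), so the change applies only to patients still to be enrolled and needs ethics approval under the amendment section {25}.

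No sample-size figure changes.

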### Who will take informed consent? {26a}

A member of the study team will check eligibility and obtain written informed consent after explaining the study and answering any questions during a visit to the research site for the baseline assessment. No study operations will take place until consent is provided.

### Additional consent provisions for collection and use of participant data and biological specimens {26b}

Individuals who choose to participate in the study will be asked to give permission for long-term monitoring of their electronic medical records (with no additional patient contact). Permission will be obtained to utilize study data in other ways, such as for pooled analyses of anonymized data, natural history studies, meta-analyses, and health outcomes research.

## Interventions

### Explanation for the choice of comparators {6b}

After CE, the lack of endothelium leads to activation of the coagulation cascade [18–20]. Therefore, antithrombotic treatment is required [20]; however, no standard protocol exists. Heparin infusion followed by warfarin for several months has been recommended by several authors [21, 22]. Pre- or intraoperative clopidogrel dosing followed by postoperative aspirin and clopidogrel administration is another anticoagulation scheme which has been used [22]. In our hospital, we have used a postoperative heparin infusion followed by DAPT (aspirin and clopidogrel or ticagrelor) for many years. Tirofiban infusion followed by DAPT is another potential regimen which is purely antiplatelet in nature.

## Intervention description {11a}

### Standard procedure before randomization

Before surgery, patients hospitalized for isolated CABG will receive the following standard antithrombotic regimen: aspirin will be administered up to the day of the procedure; clopidogrel, ticagrelor, and prasugrel will be stopped at least 5, 5, and 7 days before, respectively.

CE-CABG will be performed by experienced surgeons via a median sternotomy utilizing either an on- or off-pump grafting technique. CE will be indicated for patients with: (1) a long, diffusely diseased coronary artery segment or severely calcified coronary artery, or (2) severe long-segment in-stent restenosis with or without major side branch occlusion [23]. CE is occasionally unanticipated prior to CABG surgery. CE-CABG is typically the last option for obtaining full revascularization. Patients who do not undergo CE have a better prognosis than those that do when antithrombotic medication is used according to current recommendations; therefore, they are not required to receive tirofiban therapy and will not be included.

Graft flow and PI will be assessed at the end of the operation before protamine administration using the VeriQ Flowmeter System (MediStim ASA, Horten, Norway), which is based on an ultrasonic transit time flow meter. If the PI is more than 5, the graft must be anastomosed again. If it remains above 5, the surgery is deemed a failure and the patient will be removed from the study.

After the procedure, protamine will be administered to reverse the heparin (100 IU heparin: 1 mg protamine) and the active coagulation time will be corrected to the pre-heparinization value of 5%. Chest tube blood loss will be evaluated 2 h after surgery; if < 150 mL, the patient will be randomized.

### Randomization and intervention

Eligible patients will be randomized to either the heparin or tirofiban group in a 1:1 ratio utilizing an interactive online response system. Using the biased-coin minimization approach, a static randomization list will be created and applied taking three strata into consideration: research site, patient age group (< 70 and ≥ 70 years), and gender. Figure 1 depicts the enrollment and randomization procedures.

